### Sample size

To address the primary aim based on the assumption to detect a medium effect size of 0.4 standard deviation (equivalent to approximately a one-unit change in BMI) in changes of circadian behavior or metabolic health indicators from baseline to 3-month, we calculated that a sample size of 198 females is required. This sample size is supported by findings from previous trials that employed the healthy plate concept or a digital intervention alone, both components of the HELMS intervention, which demonstrated significant reductions in BMI exceeding one unit over a 3-month period [32, 33]. The calculation was based on achieving 80% statistical power and maintaining a two-sided type I error rate of 5%, under the assumption that 50% of the cohort will become pregnant within the year. To account for a potential 30% incomplete 3-month follow-up (including an estimated 15% pregnancy rate within 3 months) and parameter uncertainty, we will enroll a total of 283 participants.

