### HELMS integrated lifestyle intervention

HELMS is conceptualized as a new model-of-care that employs an early life course approach through a mobile health platform to transform maternal and child health in Singapore [15]. The HELMS study is designed as an implementation trial to assess the efficacy of this innovative model in optimizing the metabolic and mental health of females with overweight or obesity throughout the preconception, pregnancy, and postpartum periods. Details of the HELMS protocol have been published elsewhere [14]. In brief, the intervention components specific to the preconception phase, which are similarly experienced by all TEMPO participants, include the following: After initial baseline assessments, each participant consults a doctor who provides in-person consultations and prescribes micronutrient supplements. The HELMS mobile app is introduced to provide educational materials on self-care, sexual health, and healthy lifestyles. Equipped with feedback and goal-setting functions, the app utilizes participants’ data inputs to generate reports and recommendations, guiding them towards a healthier behavior. Weekly motivational nudges are sent via the app throughout one year of conception attempts to offer anticipatory guidance in preconception care and encourage healthy lifestyle habits.

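### The 0.4 SD behind the sample size is supported by BMI falls over time, not by a difference between women who do and do not conceive, and 283 contains no allowance for parameter uncertainty

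*Protocol article*

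**What the plan says.** All the figures are in the Sample size section of the protocol article.

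- **Target.** The aim is to detect 0.4 SD in the change from baseline to 3 months, described as "equivalent to approximately a one-unit change in BMI". Power is 80% and the two-sided type I error rate is 5%. On this basis "we calculated that a sample size of 198 females is required".
- **Support for the effect.** Earlier trials of the healthy plate concept or of a digital intervention alone, both components of HELMS, are cited as trials "which demonstrated significant reductions in BMI exceeding one unit over a 3-month period".
- **Outcome split.** The calculation is made "under the assumption that 50% of the cohort will become pregnant within the year".
- **Inflation.** The total of 283 is reached "To account for a potential 30% incomplete 3-month follow-up (including an estimated 15% pregnancy rate within 3 months) and parameter uncertainty".

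Two other sections matter. The section on the HELMS integrated lifestyle intervention describes preconception components "which are similarly experienced by all TEMPO participants". The Statistical analysis plan section limits the primary analysis to women who complete the 3-month visit. It relates clinical pregnancy to the z-scored change by modified Poisson regression.

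**The concern.** The study asks whether women whose circadian or metabolic indicators change more are more likely to conceive. The quantity that drives its power is how far the 3-month change differs between women who conceive and women who do not. The evidence offered for 0.4 SD concerns something else, namely how far mean BMI falls over three months under intervention. If every woman's BMI fell by one unit, the cited result would be reproduced exactly and the difference between the two groups would be zero.

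The paragraph also tells the reader that the enrolment figure contains a cushion for wrong assumptions. If that cushion does not exist, the study has no protection on the very parameter that is least well supported. The 80% would then be taken as firmer than it is.

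**Working it through.** **1. Reproduce 198.** Inputs from the Sample size section: d = 0.4, two-sided 5%, 80% power, 50% pregnant (1:1 split).

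- Normal approximation, total: 4 x (1.96 + 0.8416)² / 0.4² = 196.2. This is 98.1 per group, rounded up to 99, or 198 in all.
- t-based solution: 99.08 per group. Power at 99 per group is 80.0% (80.4% by normal approximation).
- A one-sample pre-post test at 0.4 SD needs (1.96 + 0.8416)² / 0.4² = 49.1, so 50 women.

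The article does not name the test. The match to 2 x 99 and the 50% pregnancy assumption show that it is a two-group comparison by conception status, not a pre-post calculation.

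**2. Compare the effect with its support.** The calculation needs a difference in mean change between conceivers and non-conceivers. The cited support is a mean change over time in intervention trials. Since all participants receive the intervention, the second does not inform the first.

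**3. How much depends on 0.4 SD.** Power = Φ(d x √(99/2) − 1.96), with √(99/2) = 7.036. The smaller values of d are illustrative, because the article gives no basis for choosing one.

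| True difference (SD) | Power, 99 per group |
|---|---|
| 0.40 | 80% |
| 0.35 | 69% |
| 0.30 | 56% |
| 0.25 | 42% |
| 0.20 | 29% |

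**4. Reproduce 283.** 198 / (1 − 0.30) = 282.86, rounded up to 283. The 30% loss consumes the whole inflation and the allowance for parameter uncertainty is zero. If the loss were 35% or 40%, 183 or 169 women would remain, with power of 77% or 74% at 0.4 SD and a 1:1 split.

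**5. The pregnancy share among those analysed.** Of 100 enrolled, 50 are assumed to conceive in the year. The 15 who do so within 3 months are counted as incomplete.

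- Other losses unrelated to conception (assumption): (50 − 15)/(100 − 15) = 35/85 = 41.2%, about 81.5 against 116.5 of 198. Power at 0.4 SD is 78.7% by t-test. By normal approximation it is Φ(0.4 x √(198 x 0.412 x 0.588) − 1.96) = 79.1%.
- The other 15 all non-conceivers (assumption): 35/70 = 50%, and nothing is lost.
- The other 15 all women who would have conceived later (an extreme assumption): 20/70 = 28.6%, and Φ(0.4 x √(198 x 0.286 x 0.714) − 1.96) = Φ(0.58), about 72%.

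**6. Does the power carry over to the primary model?** Unadjusted modified Poisson regression with robust standard errors was simulated with 198 women, a true 0.4 SD difference and 3,000 runs. Power was 80.5% at a 50% share, with a risk ratio (RR) of about 1.22 per SD. At 41.2% it was 80.0%, with an RR of about 1.26 per SD.

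**The case against.** The strongest reply is that the arithmetic is sound and fits the planned analysis. Both 198 and 283 reproduce. At a true difference of 0.4 SD the power transfers to the unadjusted modified Poisson model, and removing early conceptions costs about one point under the natural assumption. All of this stands.

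A reader might infer from the BMI rationale that the study was sized as a pre-post comparison, or that the 80% does not apply to the primary analysis. The documents support neither reading. A pre-post calculation would need about a quarter of the stated number, and step 6 shows the power carrying over.

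A reader might also try to put a lower figure on the power of the covariate-adjusted model, or of an analysis with missing 12-month outcomes. That would need the share of exposure variance explained by covariates and a late-loss rate, and the article gives neither. It does plan a 9-month call, retrieval of outcomes from medical records and multiple imputation. Leaving such detail to the full plan is normal for an article and is not criticised here. Nor is the SD of BMI change implied by the one-unit equivalence (1/0.4 = 2.5 kg/m²), because power depends only on the 0.4.

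Finally, the earlier trials can fairly be cited to show that a one-unit change is attainable in three months, so that the exposure has room to vary. That is a legitimate use, but not the one the paragraph makes of them.

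**Conclusion.** The point holds in a limited form. The 80% power is a conditional statement. It applies to an unadjusted analysis of 198 completers if the change truly differs by 0.4 SD between women who do and do not conceive. The article offers no evidence for that difference, since the cited BMI falls measure something else. The claimed allowance for parameter uncertainty is zero, and this follows from the stated figures without any assumption.

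The first matter has the larger consequence: power falls to 56% if the difference is 0.30 SD, an illustrative value. The 50% share is a minor inconsistency, worth about one point if other losses are unrelated to conception. It would matter more only if they fell mainly on women who would later have conceived, which nothing in the article suggests.

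This is a fault in how the power is justified and described. It is not a reason to enlarge the study, and it does not show that the primary analysis is mismatched to the calculation.

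**What to change.** Rewrite the Sample size paragraph and leave enrolment at 283.

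1. State that the 80% (about 79% at a 41% pregnancy share among completers, if other losses are unrelated to conception) is conditional on a true 0.4 SD difference in 3-month change between conceivers and non-conceivers. Say that it refers to the unadjusted analysis of 198 completers and corresponds to an RR of roughly 1.2 to 1.3 per SD.
2. Relabel the earlier-trial BMI falls as evidence that a one-unit change is attainable, or replace them with evidence on the between-group difference. Add power for smaller differences, as in the table above, marked as illustrative.
3. Delete the reference to parameter uncertainty, since 283 covers the 30% loss and nothing else.

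The cost is one reworded paragraph. The drawback is that the stated basis for the power looks less favourable than it does now.

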### Outcomes and assessments

The primary outcome of the study is the clinical pregnancy rate, defined as the probability of successful conception within 12 months from enrolment, whether spontaneous or through assisted reproductive technology. A clinical pregnancy is confirmed by a positive urinary pregnancy test followed by the detection of an intrauterine gestational sac after six weeks of amenorrhea via an ultrasound scan [12]. If an ultrasound scan is not available or inconclusive, the diagnosis of pregnancy will be made clinically. Biochemical pregnancy is not counted as a pregnancy event [27].

The secondary outcome, fecundability, is defined as the probability of conceiving during a normal menstrual cycle with unprotected intercourse [28]. It is measured by the time-to-pregnancy in menstrual cycles, consistent with methodologies described in our previous studies [8, 12, 27]. Specifically, we calculate the interval between the date of the last menstrual period at recruitment (baseline) and before conception (for those who became pregnant within one year) or the last follow-up call (for those who did not conceive or withdrew from the study). This interval is then converted into menstrual cycles by dividing by the average cycle length. The number of months attempting to conceive prior to study entry is considered in the computation of time-to-pregnancy. Monthly menstrual and coital histories captured over the study period are used to determine the cycle length and the cycle-at-risk, minimizing the risk of overestimating the number of cycles at risk in the absence of sexual intercourse.

In addition, live birth rates will be tracked as a downstream reproductive outcome through linkage with medical records among participants who achieve clinical pregnancy.

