### Statistical analysis plan

We will perform statistical analyses using the Stata Statistical Software. The primary exposure of interest in this study is the change in circadian behavior and metabolic health indicators over the first 3 months of the preconception period. Although the HELMS program continues throughout preconception, pregnancy, and the postnatal period, this initial 3-month interval is pre-specified in TEMPO as the primary exposure window. This interval was selected to allow sufficient time to capture measurable changes in circadian behaviors and metabolic indicators before pregnancy-related changes occur and before substantial loss to follow-up. Accordingly, only participants who complete the 3-month assessment have a fully characterized exposure and are included in the primary analysis, ensuring correct temporal ordering between exposure assessment and subsequent reproductive outcomes.

To investigate changes in circadian behavior and metabolic health indicators between baseline and the 3-month follow-up as exposure variables, the primary analysis will include only participants who have completed the 3-month visit. To identify any potential selection bias, we will compare baseline characteristics between participants included in and excluded from the primary analysis, as well as those recruited into the TEMPO and HELMS studies alone. We will use Pearson’s chi-squared test for categorical variables and either independent t-test or Mann-Whitney U test for continuous variables.

We will examine the associations of changes in circadian behavior and metabolic health indicators with pregnancy rates using modified Poisson regression models. These models will estimate risk ratios and 95% confidence intervals, adjusting for potential covariates identified from the literature and using a directed acyclic graph [6, 12, 29, 30]. Changes in these indicators will be standardized to z-scores to facilitate comparison of the relative impacts of each exposure indicator. These indicators will be treated either as continuous or categorical exposures (e.g. by tertiles or quantiles). Sensitivity analyses will re-evaluate models with spontaneous conception and live birth as the outcomes.

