Several limitations exist within this study. Due to its observational nature, the study may not definitively establish causal relationships between circadian and metabolic changes and reproductive outcomes. The reliance on self-reported data for certain lifestyle factors and circadian behaviors may introduce reporting biases. We are mitigating these biases by integrating data from digital wearables and diary records to validate and strengthen self-reported information. This multifaceted approach will not only confirm findings but also facilitate the practical application of screening tools derived from questionnaires for broader use in future. The loss to follow-up may introduce selection biases. We are minimizing dropout rates through several strategies, including maintaining good communication and rapport with participants, providing incentives for time reimbursement and continued participation, and offering home visit options if necessary. Additionally, while recruitment is limited to Singapore, the ethnically diverse sample may offer insights applicable to other Asian populations, though broader generalizability will require further validation.

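### The stated 80% power assumes that no woman's 12-month pregnancy status is lost after month 3, because the enrolment allowance covers only non-completion of the 3-month assessment

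*Protocol article*

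**What the plan says.** The Sample size section of the protocol article sets out to "detect a medium effect size of 0.4 standard deviation (equivalent to approximately a one-unit change in BMI") with 80% power at a two-sided 5% level, "under the assumption that 50% of the cohort will become pregnant within the year". From this, "we calculated that a sample size of 198 females is required". Enrolment is then raised to 283, for this reason: "To account for a potential 30% incomplete 3-month follow-up (including an estimated 15% pregnancy rate within 3 months) and parameter uncertainty".

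Under Outcomes and assessments, the clinical pregnancy rate is the primary outcome, "defined as the probability of successful conception within 12 months from enrolment".

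The Statistical analysis plan section restricts the primary analysis to women who complete the 3-month visit. It justifies the 3-month exposure window partly as falling "before pregnancy-related changes occur and before substantial loss to follow-up". The same section censors women lost to follow-up in the discrete-time fecundability model, which serves the secondary outcome. It states no counterpart for the modified Poisson model of the primary outcome.

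The limitations in the Discussion add: "The loss to follow-up may introduce selection biases".

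**The concern.** The two groups behind the calculation are women who do and do not conceive within the year. Placing a woman in either group requires her status at month 12, not only her attendance at month 3. The 30% allowance is defined by the 3-month assessment. It delivers 198 women with a measured exposure but makes no provision for those who attend at month 3 and then drop out of contact without a recorded conception.

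Taken literally, the calculation assumes zero outcome loss over the nine months from month 3 to month 12. The justification of the exposure window implies that loss does occur in that period.

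At stake is how the result is read. If some 12-month outcomes are missing, the study has less than the stated power at 0.4 SD, and a null finding judged against 80% would be taken as stronger evidence of no association than it is.

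**Working it through.** **Inputs.** From the Sample size section: difference d = 0.4 SD, two-sided alpha 0.05, power 80%, 50% conceiving within the year (equal groups), 30% incomplete at 3 months. The loss of outcome between months 3 and 12, called L and expressed as a share of three-month completers, is not given. It is assumed here to lie between 5% and 20%.

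**Step 1: reproduce 198.** For two equal groups, n per group = 2(1.960 + 0.842)²/d² = 2 × 7.85/0.16 = 98.1, rounded up to 99. Total 198, as stated. With 99 per group, power is 79.97% by the noncentral t distribution (80.4% by the normal approximation).

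**Step 2: reproduce 283.** 198/(1 − 0.30) = 282.9, rounded up to 283. In reverse, 283 × 0.70 = 198.1. The division by 0.70 accounts for the whole increase, so the parameter uncertainty named in the same sentence adds nobody.

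**Step 3: apply later loss.** With enrolment held at 283, the number with a known 12-month outcome is N = 198(1 − L). Power is recomputed by the noncentral t with N/2 per group, d = 0.4 and two-sided 5%. The effect detectable with 80% power is approximately 0.40/√(1 − L).

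| Assumed L | N with known outcome | Power at 0.4 SD | Detectable effect |
|---|---|---|---|
| 0% | 198 | 80.0% | 0.40 SD |
| 5% | 188 | 77.9% | 0.41 SD |
| 10% | 178 | 75.7% | 0.42 SD |
| 15% | 168 | 73.2% | 0.43 SD |
| 20% | 158 | 70.6% | 0.45 SD |

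For example, at L = 15%: 198 × 0.85 = 168.3, and 0.40/√0.85 = 0.434.

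**Step 4: a milder pattern.** The table spreads loss evenly over the two groups. If loss fell only on the not-pregnant group (99 against 99(1 − L), with L now a share of that group), power by the normal approximation would be 78.2% at L = 10% and 75.6% at L = 20%. The baseline on that approximation is 80.4%. The direction is unchanged and the shortfall is smaller.

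**The case against.** The arithmetic is correct as stated, and both figures reproduce. The dispute is only about what the 30% covers. Four counter-arguments deserve weight.

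- **Follow-up of pregnancy status is lighter than the 3-month visit.** Table 1 lists pregnancy status at all five time points. Study procedure and Figure 2 describe prompt reporting of positive tests, a 9-month call, a 12-month review, and retrieval of outcomes from records after a positive test. The Discussion adds incentives and home visits. This stands as a reason to expect modest loss, and at 5% the cost is only about 2 power points. It does not establish complete ascertainment of women who stop responding.
- **The 30% is only a potential figure.** If 25% were incomplete at 3 months, 283 × 0.75 = 212 would remain and about 6.7% later loss could be absorbed. At 20%, 226 would remain and about 12.5% could be absorbed. This is true, but it means that the plan's own assumption proves too pessimistic; on the assumption as stated there is no reserve.
- **Missing-data methods cover it.** The plan offers multiple imputation, a separate missing category, or exclusion of a variable. None of these restores much information when the primary outcome itself is missing. Censoring helps only the secondary fecundability analysis.
- **The study is observational and meant to generate hypotheses.** This limits the consequences, but a stated power should still carry its condition.

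Two stronger readings are tempting and should be resisted. A reader might infer that the plan expects most of its attrition after month 3. The clause about the exposure window gives no rate and makes no such comparison. A reader might also carry the 15% non-pregnancy incompletion of the first three months forward as a quarterly loss rate. That 15% is failure to complete a 3-month assessment, which Patient and public involvement describes as an additional physical visit with further blood collection. It is not unknown pregnancy status, and it does not transfer to later loss of the outcome.

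**Conclusion.** The point holds as a conditional one. The stated 80% power at 0.4 SD is correct for 198 three-month completers who all have a known 12-month pregnancy status. Enrolling 283 with 30% incomplete at 3 months yields those 198 and no more, while the protocol itself implies substantial loss to follow-up after that point.

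The size depends on a rate the document does not give. Over an assumed 5% to 20% loss, power falls to between about 78% and 71%, and the detectable effect rises to between 0.41 and 0.45 SD. These figures keep the planned 50:50 split and the 0.4 SD effect, and they treat the loss as a reduction in information only, without bias. The documents do not show that power will fall short by any particular amount. They show that the quoted power rests on an unstated assumption at odds with the plan's own account of follow-up.

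**What to change.** Reword the Sample size section so that it says three things:

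- 283 enrolled is expected to give about 198 women who complete the 3-month assessment.
- 80% power at 0.4 SD presumes that the 12-month pregnancy status of all these women is known.
- Power, or the effect detectable with 80% power, is given at the sponsor's own expected loss of outcome between months 3 and 12. If no estimate is available, the 5% to 20% range above can be shown.

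The cost is a few sentences and a slightly less favourable stated power. Enrolment, data collection and analysis need not change.

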### Data management

To ensure data quality and minimize missingness, the study will employ a three-tiered data checking procedure. The first tier, using algorithms in the RedCap platform, detects outliers and missing data, serving as an early alert system for the clinical research staff to immediately address potential errors during participant visits. The second tier involves monthly monitoring of home diary records through Excel tracking logs. Any identified missing or suspicious data will be addressed during reminders or follow-up calls with participants. The third tier includes quarterly or ad-hoc data cleaning using statistical approaches, incorporating verification against medical records, clinical justifications, and team discussions for quality assurance.

